#### Main analyses

Spearman’s or Pearson’s correlations will determine relationships between variables and chi-squared analyses will be used to compare rates data. For the main group differences and time-based analyses, data will be analysed using intention-to-treat principle and then repeated with per protocol subsamples, for sensitivity analyses. For the main continuous outcome measures (HbA1c and CHD risk data) and secondary outcomes 3 x 3 mixed analysis of covariance (ANCOVA) controlling for existing group differences on key process variables will be conducted for each outcome, with post hoc comparisons using Sidak’s correction. Should the data meet the criteria for multi-level modelling, these analyses will be conducted in lieu of ANCOVA.

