### Primary outcomes

*HbA1c.* Change in blood glucose control as measured by glycated haemoglobin (HbA1c) will be recorded from patient’s medical records. HbA1c reflects average plasma glucose concentration over an 8–12-week period and will be collected at baseline and 6 and 12 months post-baseline.

*UKPDS risk.* Ten-year risk of CHD defined as fatal, and non-fatal, MI will also be calculated at baseline and 6 and 12 months post-baseline using the UKPDS risk engine (v2.0) [28]. UKPDS is a risk calculator specifically for people with type 2 diabetes. Percentage risk is calculated from participants’ age, years since diabetes diagnosis, presence of atrial fibrillation, reported smoking behaviour, sex, ethnicity, HbA1c, systolic BP, and total and HDL cholesterol.

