### Secondary outcomes

#### Clinical

The following clinical measures will also be recorded from participant’s medical records at baseline, and 6 and 12 months post-baseline to be considered independently: (i) sitting systolic and diastolic BP, (ii) total cholesterol, (iii) HDL cholesterol, and (iv) BMI.

If available in patient records, the following additional measures will also be recorded: (i) smoking status, (ii) blood glucose fasting sample, (iii) low-density lipoprotein (LDL) cholesterol, (iv) triglycerides, (v) serum creatinine, (vi) estimated glomerular filtration rate (eGFR), (vii) urine albumin to creatinine ratio (urine ACR), (viii) foot risk assessment, and (ix) impotence.

The following self-reported behavioural, cognitive and psychological measures will be measured at baseline, immediately post-intervention (approximately 3 months post-baseline), and 6 months and 12 months post-baseline.

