### Power calculation

A clinically important change in HbA1c level of 12.5 % (SD 15.5 %) was identified from a Health Technology Assessment of blood glucose monitoring devices [35] over a period of 18 months. This represents a reduction in HbA1c (%) from 8 to 7 or from 9 to 7.9. As the current study has a shorter follow-up, we base our sample size calculations on a conservative change that would be clinically achievable in this time frame: an HbA1c change of 6.25 % representing a reduction from an HbA1c (%) of 8 to 7.5 or from 9 to 8.44 (this represents a change from 63.9 mmol/ml to 59.9 mmol/ml; and 74.9 mmol/ml to 69.4 mmol/ml).

The expected 6.25 % change in HbA1c (SD = 15 %) represents an effect size of d = 0.40, a small to moderate effect size (d = 0.2 – small, 0.5 – medium and 0.8 – large effect); equivalent to effect size f = 0.2 in G*Power [36] calculated for repeated measures, between-subjects analysis of variance (ANOVA) analyses. Based on the current design (three groups, four measurement points), alpha = 0.05, power = 80 %, f = 0.20 and a correlation between measurement points of 0.70, G*Power indicates a total sample size of 192. With an expected attrition rate of 20 %, a sample size of 240 (80 per study arm) will be sought.

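### The 3 x 3 mixed ANCOVA makes baseline an outcome level for HbA1c and CHD risk, picks covariates from observed arm differences, and cannot fit the questionnaire outcomes on the same terms

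*Protocol article*

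**What the plan says.** Main analyses assigns one model to every continuous outcome. "For the main continuous outcome measures (HbA1c and CHD risk data) and secondary outcomes", a "3 x 3 mixed analysis of covariance (ANCOVA) controlling for existing group differences on key process variables will be conducted for each outcome". Sidak-corrected post hoc comparisons follow, and multi-level modelling replaces the ANCOVA if the data meet criteria that are not given.

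The measurement schedule differs by outcome:
- HbA1c "will be collected at baseline and 6 and 12 months post-baseline" (Primary outcomes).
- UKPDS risk "will also be calculated at baseline and 6 and 12 months post-baseline using the UKPDS risk engine" (Primary outcomes).
- The self-reported behavioural, cognitive and psychological measures are "measured at baseline, immediately post-intervention (approximately 3 months post-baseline), and 6 months and 12 months post-baseline" (Secondary outcomes, Clinical).

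The Power calculation section sizes the trial for "repeated measures, between-subjects analysis of variance (ANOVA) analyses" with "three groups, four measurement points", using "f = 0.20 and a correlation between measurement points of 0.70".

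**The concern.** There are three linked problems.

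1. **Baseline as an outcome.** With three occasions for HbA1c and UKPDS risk, a 3 x 3 layout puts baseline among the repeated measures. Randomisation makes the expected arm difference zero there. A group main effect is then diluted by a point with no effect, and the group x time test spreads the effect over 4 degrees of freedom.
2. **Covariates picked from the data.** The rule adjusts for unnamed process variables on which the arms differ. In a randomised trial such differences at baseline are due to chance, so the estimate and p-value for the primary outcomes would depend on which ones happen to appear. The covariate most likely to predict follow-up, the outcome's own baseline value, is not fixed.
3. **One layout for two schedules.** The same 3 x 3 is assigned to outcomes measured on three and on four occasions.

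At stake are the power of the primary comparisons and whether their model is settled before the data are seen.

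**Working it through.** **Layout against schedule**

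| Handling of baseline | HbA1c, UKPDS risk (baseline, 6, 12 months) | Questionnaires (baseline, 3, 6, 12 months) |
|---|---|---|
| Time level | 3 x 3 | 3 x 4 |
| Covariate | 3 x 2 | 3 x 3 |

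Neither row gives 3 x 3 in both columns. For the primary outcomes, only the first row matches the text.

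**The plan's own figure**

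Inputs from Power calculation: k = 3 groups, m = 4 occasions, f = 0.20, rho = 0.70, alpha = 0.05. For the between-subjects effect, lambda = f² N m / (1 + (m − 1) rho), with k − 1 and N − k df. At N = 192, lambda = 0.04 × 192 × 4 / 3.1 = 9.91 and power is 0.805, so 192 reproduces. 192 / 0.80 = 240 also reproduces. With the three occasions HbA1c actually has, power at 192 is 0.79 and 198 are needed. This formula takes the arm difference as present at every occasion, baseline included.

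**Power with equal expected baselines**

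From the document: 192 / 3 = 64 per arm, rho = 0.70, d = 0.40. Assumed here: SD 1 at each occasion, compound symmetry, d = 0.40 as the largest arm difference, and no gain from the unnamed covariates.

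The arm sum of squares is 0.08 for evenly spaced arms (0, 0.2, 0.4) and 0.1067 for one arm differing from the other two. Multiplied by 64, this gives A = 5.12 or 6.83. Each range below runs from the first pattern to the second.

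Constant effect at 6 and 12 months (time profile 0, 1, 1):
- Group main effect over three levels: the mean profile is 2/3 and the variance of the three-occasion mean is (1 + 2 × 0.70)/3 = 0.80. lambda = A × 0.444 / 0.80 = 2.84 to 3.79; df 2, 189; power 30-39 %.
- Group x time: the sum of squared deviations of the profile is 0.667 and the within-person variance is 1 − 0.70 = 0.30. lambda = A × 0.667 / 0.30 = 11.38 to 15.17; df 4, 378; power 77-89 %.
- Baseline-adjusted ANCOVA, mean of 6 and 12 months: residual variance (1 + 0.70)/2 − 0.70² = 0.36. lambda = A / 0.36 = 14.22 to 18.96; df 2, 188; power 93-98 %.
- Baseline-adjusted ANCOVA, 12 months alone: residual variance 1 − 0.70² = 0.51. lambda = A / 0.51 = 10.04 to 13.39; df 2, 188; power 81-91 %.

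Half the effect at 6 months, full at 12 (profile 0, 0.5, 1):
- Group main effect: lambda = A × 0.25 / 0.80 = 1.60 to 2.13; power 18-24 %.
- Group x time: lambda = A × 0.5 / 0.30 = 8.53 to 11.38; power 63-77 %.
- ANCOVA, 6/12-month mean: lambda = A × 0.5625 / 0.36 = 8.00 to 10.67; power 71-84 %.
- ANCOVA, 12 months: unchanged at 81-91 %.

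**The case against.** The strongest reply is that a group x time test in a mixed design is a legitimate test of differential change in a randomised trial. It causes no bias and no inflation of type I error, and its 77-89 % sits around the planned 80 %. That stands: baseline as a time level costs efficiency, not validity.

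The size of the gain also depends on the pattern of effect. Under a constant effect, ANCOVA at 12 months alone gains only 2 to 4 points over group x time. The larger gain of 9 to 16 points belongs to the 6/12-month mean, and it shrinks to 6 to 8 points if the 6-month effect is half-size. The document states no time pattern.

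A reader might infer that the trial really has only 30-39 % power. The document does not support this: Main analyses covers both group differences and time-based analyses and does not make the main effect the deciding test. The figure stays relevant because the sample size was built on a between-subjects effect.

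A reader might also infer that the covariates include post-baseline mediators, which would adjust away part of the effect. The wording speaks of existing differences, most naturally those at baseline, and nothing says that mediators are adjusted for.

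Finally, a multi-level model could take three or four occasions. But its trigger is unstated and depends on the data, and the text does not say how it would treat baseline. A separate analysis plan could name covariates, but it would have to depart from the rule printed here.

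**Conclusion.** The point holds and should be fixed. Three defects follow from the text: baseline must be an outcome level for the primary outcomes, one 3 x 3 cannot fit the clinical and questionnaire outcomes alike, and covariates are selected by observed arm differences while the outcome's own baseline value is not a fixed term.

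The efficiency loss is moderate if group x time decides and severe only if the group main effect does. Main analyses leaves that choice open. These sizes rest on the document's correlation of 0.70 and d = 0.40, and on the assumed compound symmetry and arm and time patterns. Baseline-adjusted ANCOVA had the higher power in both time patterns tried, by 2 to 18 points over group x time depending on pattern and endpoint.

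**What to change.** - Model post-baseline values only: 6 and 12 months for clinical outcomes; 3, 6 and 12 months for questionnaires.
- Pre-state the terms: arm, time, arm x time and the baseline value of the outcome analysed.
- Name the arm contrast, and the time point or follow-up mean at which it is taken, as the deciding test. Keep the Sidak-corrected pairwise comparisons.
- Delete the clause that adjusts for existing group differences on process variables.
- Optionally add randomisation cohort as a term. 240 / 15 gives about 16 cohorts, hence about 15 degrees of freedom. Taking 188 residual df to 173 leaves power for the 6/12-month mean at 93-98 %, before any reduction in variance.

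The cost is a change of analysis wording. No further participants, visits or measurements are needed, but it should be settled before the data are analysed.

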**Discussion:**

This study will determine whether the addition of personalised genetic- and lifestyle-associated CHD risk information to a group self-management intervention improves diabetes control and CHD risk compared with group self-management and usual care. Effectiveness of the combined intervention on health behaviours cognitions theorised to predict them, and psychological outcomes will also be investigated.

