### Randomisation and blinding

Participants will be randomised at the individual level using randomly permuted blocks. The randomisation sequence will be generated using a randomisation website [25]. Blocks of 15 allocations will be generated with a 1:1:1 ratio of study arm allocations to ensure a balance of five participants per study arm for each cohort. Each cohort of 15 participants will comprise patients recruited from a single GP practice site, or a single hub and spoke site grouping. Randomisation allocation will be concealed in consecutively numbered opaque sealed envelopes. As with all studies of this type it is not possible to blind participants, the recruiting nurse, or intervention facilitators to group allocation once the envelope has been opened. The data will be analysed by a researcher blinded to the allocation of the groups.

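### Sidak's correction for the three arm pairs is valid but gives up pairwise power that a closed or step-down test would recover at the same 5 % family-wise error, provided one analysis time is named

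*Protocol article*

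**What the plan says.** The Main analyses section of the protocol article specifies a "3 x 3 mixed analysis of covariance (ANCOVA) controlling for existing group differences on key process variables", which "will be conducted for each outcome, with post hoc comparisons using Sidak’s correction". It does not state how many comparisons form the family, what level each comparison gets, whether the comparisons wait for a significant overall test, or which test in the arm-by-time model would be that overall test.

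The questions the trial asks are pairwise. The abstract's Discussion says the study will determine whether adding risk information to self-management "improves diabetes control and CHD risk compared with group self-management and usual care". Study aims sets the intervention, with and without risk information, against usual care.

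The Power calculation section sizes the trial for the overall between-arm F test only, with "alpha = 0.05, power = 80 %, f = 0.20 and a correlation between measurement points of 0.70". Primary outcomes places HbA1c and UKPDS risk at baseline, 6 and 12 months and does not single out one of these times.

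**The concern.** The answers the trial wants are the arm pairs, but the sample size covers only the overall test. The pairwise rule therefore largely decides whether a real difference between two arms is declared.

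Sidak sets one level for all three pairs, as if all three nulls might be true whatever the data show. With three arms that is more protection than is needed. If any two pairwise nulls are true, all three arms are equal, so exactly one true pairwise null is possible only when the third arm differs. The intersections of the pairwise nulls therefore reduce to one hypothesis, that all arms are equal. By the closure principle, testing that hypothesis at 5 % and then each pair at 5 % holds the family-wise error strongly at 5 %. What is at stake is pairwise power that needs no further participants.

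**Working it through.** **Inputs.** Three arms, 1:1:1 (Randomisation and blinding). From Power calculation: alpha 0.05, f = 0.20, d = 0.40, four measurement points, correlation 0.70, N = 192 analysed (64 per arm), 240 recruited. Assumed, because the article does not say: two-sided tests and a Sidak family of the three arm pairs.

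**The plan's own figure.** Between-arm F test: λ = f²·N·m / (1 + (m − 1)ρ) = 0.04 × 192 × 4 / (1 + 3 × 0.70) = 30.72 / 3.1 = 9.91. With 2 and 189 df the power is 80.5 %, so 192 reproduces, and 192 / 0.8 = 240.

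**Sidak level.** 1 − 0.95^(1/3) = 0.01695, about 1.7 % per pair.

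**One pair at d = 0.40.** SD of the time average = √((1 + 3 × 0.70)/4) = √0.775 = 0.880. SE of a difference = 0.880 × √(2/64) = 0.1556. Standardised difference = 0.40 / 0.1556 = 2.57.
- Sidak: critical t (189 df) = 2.409, so power ≈ Φ(2.57 − 2.409) = Φ(0.16) ≈ 56 %.
- Unadjusted 5 %: critical t = 1.973, so power ≈ Φ(0.60) ≈ 73 %. The closed test cannot exceed this, and its 2-df gate brings it somewhat lower.

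**Simulation** (400,000 trials per pattern, 64 per arm, SD 0.880). Closed = 2-df arm test at 5 %, then each pair at 5 %. Shaffer = smallest p at 1.7 %, then the other two at 5 %.

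| True means | Pair | Sidak | Closed | Shaffer | Closed gain (points) |
|---|---|---|---|---|---|
| 0/0/0.4 | each pair with the differing arm | 56.5 % | 66.8 % | 64.3 % | 10 |
| 0/0.2/0.4 | adjacent | 13.3 % | 23.2 % | 22.0 % | 10 |
| 0/0.2/0.4 | extreme | 56.4 % | 60.5 % | 58.5 % | 4 |
| 0/0.3/0.4 | extreme | 56.5 % | 62.5 % | 60.2 % | 6 |
| 0/0.4/0.8 | adjacent | 56.5 % | 72.6 % | 72.5 % | 16 |
| 0/0.4/0.8 | extreme | 99.7 % | 99.7 % | 99.7 % | 0 |

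Gating Sidak on the arm test barely matters: 56.3 % instead of 56.5 % for 0/0/0.4. Ungated Sidak rejects a pair that the closed test misses in under 1 % of trials.

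**Family-wise error.**
- All arms equal: closed 5.0 %, Sidak 4.4 %, Shaffer 4.4 %.
- Means 0/0/0.4, one true pairwise null: closed 4.9 %, Sidak 1.7 %, Shaffer 4.8 %.

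**Sensitivity to baseline adjustment.** For one follow-up adjusted for baseline, the residual SD is √(1 − 0.70²) = 0.714. For the 0/0/0.4 pattern:
- single follow-up, 64 per arm: 77.6 % to 85.7 % (8 points);
- single follow-up, 80 per arm: 87.1 % to 92.9 % (6 points);
- mean of two follow-ups: 91 % to 96 % at 64 per arm (4 points) and 96.4 % to 98.5 % at 80 per arm (2 points).

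Adjacent pairs spaced 0.2 apart still gain about 13-17 points on these scales.

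**More than one visit.** I took means 0/0/0.4 at 6 months and no effect at 12 months, with a separate 2-df arm test opening unadjusted pairs at each visit. The joint family-wise error over both visits is about 9 %, against 6 % for Sidak within each visit. If a single arm-by-time test opens unadjusted pairs at both visits, a smaller simulation (4,000 trials) gives about 15 %, against about 5.7 % for Sidak. The closed argument holds for one outcome and one arm contrast, not across visits.

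**The case against.** The strongest reply is that nothing here is stated wrongly. Sidak is standard and valid, it gives simultaneous intervals that agree with its tests, and choosing it is a legitimate trade-off. The size of the family and any gating rule may also stand in an analysis plan that is not shown. All of that stands, and it is why this is a suggested improvement. The choice of Sidak itself is written into the article, so it can be commented on.

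A reader might infer that the plan pays for multiplicity twice and gains no error control from Sidak. The document does not support this. It states neither a gate nor a 1.7 % level. When all arms are equal Sidak is only mildly conservative (4.4 %). In the planned arm-by-time model with two follow-ups, Sidak does buy some protection over unadjusted pairs, as the joint error rates above show.

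A reader might also infer a gain of 8 to 16 points in most patterns. The 16 comes from means 0/0.4/0.8, whose extreme contrast of 0.8 is twice the planned d = 0.40 and whose f is √((0.4² + 0 + 0.4²)/3) = 0.33 against the planned 0.20. The base scale also averages four points including baseline, whereas the clinical outcomes are recorded at three, and the gain for one differing arm shrinks under baseline adjustment.

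**Conclusion.** The point holds as one of efficiency. For a single outcome and a single arm contrast, Sidak is less powerful than two procedures that hold the same 5 % family-wise error. On the plan's own inputs the gain is about 10 points when one arm differs from two equal arms, and about 10 points for adjacent pairs of a 0/0.2/0.4 pattern. It is 0-6 points for the extreme pair of a graded pattern, and about 8 points down to 2 for the one-arm-differs pattern under strong baseline adjustment.

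This rests on a family of three two-sided pairs, 64 analysed per arm, correlation 0.70 and normal data. It does not show an error in the plan or an inflated error rate, and it has no bearing on multiplicity over the two primary outcomes, which the article handles outcome by outcome.

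**What to change.** For each primary outcome, name one analysis time or one averaged arm contrast. For the three arm pairs there, replace Sidak with one of:
- the 2-df arm test at 5 % and, if it is significant, each pair at an unadjusted 5 %; or
- Shaffer's step-down: the smallest p-value at 1.7 % and, if that is significant, the other two at 5 %. This needs no overall gate and never rejects less than Sidak.

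Do not let the arm-by-time test open unadjusted pairs at several visits. At other visits, keep an adjustment or label the comparisons as secondary.

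The change is a few sentences of analysis wording and needs no more participants, but the time point or contrast has to be chosen first, before unblinded analysis. Sidak's simultaneous intervals will no longer match the test decisions, so 95 % intervals should be labelled as unadjusted. Any rule for the two primary outcomes must be stated separately.

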### Study interventions

#### Self-management intervention

Participants allocated to the SMI group and the SMI + RR group will attend group self-management sessions for 4 consecutive weeks, which will be held at a local GP surgery or community practice, in addition to their usual care. Each session will last approximately 2 hours, and will be facilitated by an SMI-trained practice or research nurse with experience of providing clinical care to patients with diabetes, paired with a health psychologist researcher or layperson. Ten participants will attend each SMI group (five SMI only, five SMI + RR). The facilitator will keep an attendance log. Intervention sessions will be audio recorded where participants provide permission, to investigate intervention fidelity.

All SMI facilitators will attend a 2-day self-management training course led by two experienced self-management practitioners and trainers. The training comprises teaching regarding theories of behaviour change and self-management. Facilitators will be taught how to use the SMI manual and will practice skills for managing groups. After training they will be supported to deliver the intervention through pre- and post-session briefing meetings each week within their facilitator pairings, and with the research team.

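### The default ANCOVA leaves out the cohort and session-group clustering built into the design, and the only alternative model depends on unstated, data-dependent criteria

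*Protocol article*

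**What the plan says.** **Randomisation** (Protocol article, *Randomisation and blinding*): "Participants will be randomised at the individual level using randomly permuted blocks". The blocks hold 15 allocations at 1:1:1, "to ensure a balance of five participants per study arm for each cohort". The block is also the recruitment unit: "Each cohort of 15 participants will comprise patients recruited from a single GP practice site, or a single hub and spoke site grouping".

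**Delivery** (*Self-management intervention*): "Ten participants will attend each SMI group (five SMI only, five SMI + RR". The group meets four times under one pair of facilitators. *Usual care control group* describes no group.

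**Analysis** (*Main analyses*): for HbA1c, CHD risk and the secondary outcomes, a 3 x 3 mixed ANCOVA "controlling for existing group differences on key process variables will be conducted for each outcome", "with post hoc comparisons using Sidak’s correction". No cohort, practice or session-group term is named. The next sentence adds: "Should the data meet the criteria for multi-level modelling, these analyses will be conducted in lieu of ANCOVA". It does not state the criteria or the levels, and it does not mention clustering.

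**The concern.** The clustering is known from the design before any data exist. All three arms of a cohort share a site and a randomisation block. The two SMI arms also share a group and its facilitators. The sessions work through group problem solving, goal review and praise, so mutual influence is part of the treatment.

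An analysis that treats participants as independent gives both of the trial's questions a wrong standard error, by different amounts and possibly in different directions. The question on the added risk information (SMI + RR versus SMI) loses some power. The question on self-management against usual care may be tested at more than the nominal level. Because the move to a multi-level model depends on the data under no stated rule, the analysis of both primary outcomes is also left open.

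**Working it through.** **1. The plan's own figure.** Inputs from *Power calculation*: k = 3 groups, m = 4 measurement points, f = 0.20, correlation 0.70, alpha 0.05, power 80 %. The between-subjects repeated-measures formula is λ = f²·N·m / (1 + (m − 1)·ρ). With N = 192, λ = 0.04 × 192 × 4 / 3.1 = 9.91. On 2 and 189 degrees of freedom this gives power 0.805. Then 192 / 0.80 = 240. Both stated figures reproduce, and the formula assumes independent participants.

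**2. Structure.** 240 / 15 = 16 cohorts, with n = 5 per arm per cohort (n = 4 after the planned 20 % attrition). Five SMI plus five SMI + RR make the group of ten, so there is one session group per cohort.

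**3. Variances.** Let rc be the cohort ICC (shared by all arms) and rg the session-group ICC (shared by the two SMI arms only). The residual is e = 1 − rc − rg. True variances of a difference, per cohort (divide by 16 for the trial):

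- SMI + RR versus SMI: 2e/n. Both cluster effects cancel.
- SMI versus usual care: 2e/n + rg. The cohort effect cancels; the session-group effect does not.

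The independence analysis uses 2s²/n. Here s² is the within-arm variance pooled over three arms: s² = e + q·(rc + 2rg/3), with q = (80 − 5)/79 = 0.949 for n = 5.

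*Worked case*, rc = 0, rg = 0.05, n = 5: e = 0.95; s² = 0.95 + 0.949 × 0.0333 = 0.982; assumed variance 0.393. True variances are 0.430 (SMI versus usual care) and 0.380 (SMI + RR versus SMI). Assumed/true SE = √(0.393/0.430) = 0.956 and √(0.393/0.380) = 1.017. The actual level is 2Φ(−1.96 × ratio): 6.1 % and 4.6 %.

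**4. Range** (all ICCs assumed; n = 5; single-time-point outcome; unadjusted two-sided 5 % tests):

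| rc | rg | SMI v usual care: SE ratio, level | SMI + RR v SMI: SE ratio, level |
|---|---|---|---|
| 0 | 0.05 | 0.956, 6.1 % | 1.017, 4.6 % |
| 0 | 0.10 | 0.915, 7.3 % | 1.035, 4.3 % |
| 0.02 | 0.05 | 0.964, 5.9 % | 1.027, 4.4 % |
| 0.05 | 0.02 | 1.005, 4.9 % | 1.032, 4.3 % |
| 0.05 | 0.05 | 0.977, 5.5 % | 1.043, 4.1 % |
| 0.05 | 0.10 | 0.935, 6.7 % | 1.063, 3.7 % |
| 0.10 | 0.02 | 1.030, 4.3 % | 1.059, 3.8 % |
| 0.10 | 0.10 | 0.955, 6.1 % | 1.094, 3.2 % |

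A simulation of 15,000 trials per setting agrees: at rc = 0.05, rg = 0.10 it gave 6.75 % and 3.9 %.

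**5. When the directions differ.** With q taken as 1, the SMI versus usual care SE is too small if rg > c·rc / (1 − 2c/3), where c = 2/n. For n = 5 this is 0.4/0.733 = 0.55; for n = 4 it is 0.5/0.667 = 0.75. If every arm instead has the same total variance, the condition for n = 5 is rg > 0.5·rc. Under that assumption the levels for SMI versus usual care at rc = 0 are 6.2 % (rg = 0.05) and 7.4 % (rg = 0.10).

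**6. Attrition and Sidak.** With n = 4, the SMI versus usual care level falls from 6.1 % to 5.8 % at (0, 0.05) and from 5.5 % to 5.2 % at (0.05, 0.05). Sidak over three comparisons tests each at 1 − 0.95^(1/3) = 1.7 %; at rc = 0 and rg = 0.05 or 0.10 this becomes about 2.3 % or 2.9 %.

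**7. If the criterion were a significance test of clustering** (an assumption; the protocol names none): with 16 groups of ten, the one-way F test at 5 % has power 33 % at ICC 0.05 and 65 % at 0.10. With eight per group these are 26 % and 53 %.

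**The case against.** *A reader might infer that the two comparisons are always wrong in opposite directions.* The documents do not support that. They give no ICC, and with cohort ICC 0.05 and session-group ICC 0.02 both comparisons are conservative. Quoting SMI versus usual care only at cohort ICC 0 would show its worst case.

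*A reader might also take the conditional sentence as the rule for when clustering is modelled.* It does not say so. Its levels could be repeated measures within participants, in which case clustering would stay out even if the switch were used. Nor can one say that a test would usually reject the multi-level model: no test is described, and at ICC 0.10 one would be nearer a coin toss.

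Other points in the plan's favour stand in part:

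- The errors are modest because only five per arm share a cluster, and attrition reduces the inflation.
- The levels in the table are for unadjusted tests, whereas the plan uses Sidak. The proportional inflation remains.
- Baseline is one of the time points, so a group-by-time test removes stable site differences. Session-group effects arise after baseline and are not removed.
- The analyst is blinded to allocation, which limits steering of the model choice. It does not make the default model right.
- A condensed article may leave model details to a fuller document. But this one fixes a default without the design's structure and makes the alternative depend on the data; that is a stated choice, not an omitted detail.

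**Conclusion.** The point holds in a limited form. The default model does not follow the randomisation blocks or the shared delivery groups, and the switch away from it has no stated rule.

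The SMI + RR versus SMI standard error is too large whenever either ICC is above 0, so that test is conservative and loses some power. The SMI versus usual care standard error may be too small, depending on how session-group variance compares with cohort variance. Over the assumed range, standard errors are off by roughly 1 to 9 % in most settings (from about 9 % too small to about 9 % too large). Type I error is about 4 to 7 %, or about 3 % for SMI + RR versus SMI when both ICCs are 0.10.

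This rests on assumed ICCs, one session group per cohort, and a single-time-point outcome. Baseline adjustment would change the ICCs but not the structure. The size does not invalidate the trial, but the defect is avoidable and should be corrected before analysis.

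**What to change.** Delete the data-dependent switch. State one primary model for each primary outcome, used whatever the data show: a baseline-adjusted mixed model with

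- an effect for cohort (the randomisation block);
- a random session-group effect that applies only to participants in the two SMI arms;
- a small-sample degrees-of-freedom correction, since there are only about 16 cohorts;
- both ICCs reported with the results.

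The cost is mainly wording. Cohort is fixed by the randomisation, and the facilitators keep an attendance log. Intervals for SMI versus usual care will be slightly wider if session-group variance is material; those for SMI + RR versus SMI should narrow. A term present in only two arms would reveal the usual-care arm, so group codes must be masked, or the model code written and locked beforehand, to keep the analyst blinded to allocation.
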